## Abstract

Introduction: Patients with neurogenic lower urinary tract dysfunction (NLUTD) reliant on intermittent self-catheterization for bladder emptying are at an increased risk of recurrent urinary tract infections (rUTI). So far, the most common practice in the prevention of rUTIs is long-term low-dose antibiotic prophylaxis, phytotherapy, and immunomodulation, whereby antibiotic prophylaxis inevitably leads to the emergence of drug-resistant pathogens and difficulty in treating infections. Therefore, non-antibiotic alternatives in the prevention of rUTIs are urgently required. We aim to identify the comparative clinical effectiveness of a non-antibiotic prophylaxis regimen in the prevention of recurrent urinary tract infections in patients with neurogenic bladder dysfunction who practice intermittent self-catheterization. Methods and analysis: In this multi-centre, prospective longitudinal multi-arm observational study, a total of 785 patients practising intermittent self-catheterisation due to NLUTD will be included. After inclusion, non-antibiotic prophylaxis regimens will be instilled with either UroVaxom^®^ (OM-89) standard regimen, StroVac^®^ (bacterial lysate vaccine) standard regimen, Angocin^®^, D-mannose (oral dose 2 g), bladder irrigation with saline (once per day). The management protocols will be pre-defined, but the selection of the protocol will be at the clinicians’ discretion. Patients will be followed for 12 months from the onset of the prophylaxis protocol. The primary outcome is to identify the incidence of breakthrough infections. The secondary outcomes are adverse events associated with the prophylaxis regimens and the severity of breakthrough infections. Other outcomes include the exploration of change in susceptibility pattern via the optional rectal and perineal swab, as well as health-related quality of life over time (HRQoL), which will be measured in a random subgroup of 30 patients. Ethics and dissemination: Ethical approval for this study has been granted by the ethical review board of the University Medical Centre Rostock (A 2021-0238 from 28 October 2021). The results will be published in a peer-reviewed journal and presented at relevant meetings. Study registration number: German Clinical Trials Register: Number DRKS00029142.

## 1. Introduction

### 1.1. Neurogenic Lower Urinary Tract Dysfunction (NLUTD)

An increased risk of rUTIs is known in patients with neurogenic lower urinary tract dysfunction (NLUTD) due to the impairment in the urinary tract’s physical protective mechanisms. The cause of NLUTD and how it can manifest as a UTI are heterogeneous. Patients with NLUTD have an annual incidence of 54.9% of developing UTIs [1]. Unfortunately, most patients with NLUTD who develop UTIs will have recurrent episodes of infections followed [2]. The UTIs in this population are not only a worry for mortality and morbidity but also have a great impact on quality of life. Moreover, frequent UTIs mean that these patients get exposed to a high quantity of antibiotics, which is the main driver of the emergence of drug-resistant difficult-to-treat bacterial infections.

To break the vicious cycle of recurrent UTIs (rUTI), prophylactic measures are propagated, albeit with limited evidence to support one intervention over the other. So far, the most common practice in the prevention of rUTIs is long-term low-dose antibiotic prophylaxis, phytotherapy, and immunomodulation. The antibiotic prophylaxis option exacerbates the emergence of difficult-to-treat drug-resistant infections. Therefore, non-antibiotic alternatives in the prevention of rUTIs are urgently required. 

We have recourse to a broad armamentarium of non-antibiotic options, whereby significant evidence is limited. Several viable and readily available options have been shown to yield consistent results. Main alternatives to antibiotic prophylaxis include vaccines, antiseptics, urine-specific antimicrobials, and direct mechanic washouts of the bladder. A variety of vaccines have been used in the prevention of rUTIs. Especially OM-89 (Urovaxom^®^) and the bacterial lysate vaccine Strovac^®^ have been diligently tested and proven to lower the rate of UTI [3,4,5,6]. Additionally, a wide variety of phytotherapeutics is currently in use, especially in Eastern medicine, as a cost-effective and low-threshold, whereas ambivalent efficacy has been reported. A combination of Tropaeoli majoris herba (Nasturtium) and Armoraciae rusticanae radix (Horseradish) demonstrated excellent safety and efficacy in the prevention of recurrent UTIs [7,8]. D-Mannose is another beneficial and cheap prophylactic, therapeutic agent in rUTI with very few side effects [9,10]. Bladder irrigation with various agents, e.g., neomycin, acetic acid, or sterile saline, is also widely used in order to lower bacterial load and defer sedimentation [11,12,13]. 

The main aim of our study is to identify the comparative clinical effectiveness of non-antibiotic prophylaxis regimens in the prevention of rUTI infections in patients with neurogenic bladder dysfunction who practise clean intermittent self-catheterization (CISC). The primary outcome is depicted by the number of breakthrough infections. Secondarily adverse events associated with the prophylaxis regimens and the severity of breakthrough infections must be investigated. 

Change in susceptibility pattern via the optional rectal and perineal swab, as well as health-related quality of life over time (HRQoL) outcomes, will be measured in a random subgroup of 60 patients.

The primary objective is to identify the clinical effectiveness of different prophylactic regimens. The secondary objective is to determine the adverse events related to prophylaxis and the severity of breakthrough infections. 

### 1.2. rUTI in NLUTD

Patients unable to empty their bladder to completion due to a neurogenic disorder require adjunct management options to ensure a low-pressure urinary tract as well as sufficient emptying of the bladder. The most common way of achieving bladder emptying in patients with manual dexterity or with a carer to support is CISC. In this population, the rate of rUTI is significantly high at 9.4 episodes per year [14,15]. 

### 1.3. Definition of UTI in NLUTD

In our study, UTIs in this challenging collection of patients are defined as follows:○Positive urine culture with typical bacteria in UTI with >10^2^ CFU/mL (Colony forming units);○Urinary urgency;○Urinary frequency;○Dysuria;○Fever/chills;○Worsening of a neurological condition;○Altered mental status;○De novo incontinence.

Diagnosis of UTI is fulfilled if patients suffer from two or more of the above symptoms with positive urine culture (mandatory) [16]. 

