### 4.1. Inclusion Criteria

Microbiologically proven UTI according to Section 1.3;Age > 18;Ability to consent;NLUTD with practised ISC;rUTI (used definition: more than 3 infections per year) independent from a bacterial spectrum of infection;Failed conservative measures (e.g., an increase in fluid intake and an increase in assisted bladder emptying);Previous episodes of UTIs do not show multi-drug-resistant bacteria;Non-antibiotic prophylaxis with UroVaxom, StroVac, Angocin, D-Mannose or bladder irrigation with saline;Signed informed consent form.

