### 6.3. Evaluation at 3, 6, 9 and 12 Months (Table 1)

Number of UTI (reported by patient; if externally diagnosed and treated by, e.g., primary caregiver records will be obtained and added to study documentation);Hospital admission due to UTI or severe systemic infection (SOFA Score, SIRS criteria, Antibiotic administration, duration of hospital stays, urine culture);Antibiotic treatment/ treatment with a reserve antibiotic;Urine culture, including susceptibility profile;Rectal swab (optional);Perineal swab (optional);ACSS score;Adverse events during intake;HRQoL measures (subgroup of 30 patients);End at 12 months: patient impression (Likert Scale).

**Table 1 mps-06-00052-t001:** Summary of data collection points.

	Day 0	Month 3	6	9	12
*ACSS*	*X*	*X*	*X*	*X*	*X*
*Recruit*	*X*				
*Rectal swab*	*X ^*		*X ^*		*X ^*
*Perineal swab*	*X ^*		*X ^*		*X ^*
*CRF*	*X*	*X*	*X*	*X*	*X*
*Urine culture*	*X*		*X ^*		*X*

^ optional; ACSS = Acute Cystitis Symptom Score; CRF = Case Report Form.

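### The Section 1.3 UTI definition does not require urgency, frequency or dysuria to be new or worse, so long-standing bladder symptoms with bacteriuria can meet it without a new infection

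*Protocol article*

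**What the plan says.** Section 1.3 presents its rule as the study's own: "In our study, UTIs in this challenging collection of patients are defined as follows". The first item is the culture, "Positive urine culture with typical bacteria in UTI with >10^2^ CFU/mL (Colony forming units". Seven symptom items follow. Four are listed bare: "Urinary urgency;○Urinary frequency;○Dysuria;○Fever/chills". The other three are "Worsening of a neurological condition;○Altered mental status;○De novo incontinence". The decision rule is "Diagnosis of UTI is fulfilled if patients suffer from two or more of the above symptoms with positive urine culture (mandatory".

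The rule is used for entry, because Section 4.1 asks for "Microbiologically proven UTI according to Section 1.3". Section 3 names the rate of symptomatic breakthrough infection as the primary outcome. It does not cite Section 1.3, but the article contains no other definition of UTI.

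At 3, 6, 9 and 12 months, Section 6.3 collects a patient-reported number of UTIs (supported by outside records where another provider treated the episode), urine culture, the ACSS score and, as a separate item, "Hospital admission due to UTI or severe systemic infection". The ACSS is not linked to the definition anywhere.

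**The concern.** Within one list the authors required change for two items (neurological worsening and de novo incontinence) and left urgency, frequency and dysuria without any such requirement. In people with neurogenic bladder dysfunction, urgency and frequency may be the usual state. If so, two of the three items plus bacteriuria meet the definition on a day when nothing has changed.

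Two consequences follow for the primary comparison. First, episodes that are not new infections, and that prophylaxis cannot prevent, would dilute a real difference between regimens. Second, the error need not be equal across regimens. The abstract leaves the choice of regimen to the clinician, and Section 6.5 says assessors are not blinded. Section 5 plans to balance groups on neurological condition and prior infections but does not name baseline bladder symptoms. One regimen, saline irrigation, is described in Section 1.1 as a means of lowering bacterial load. It might therefore change how often the mandatory culture is positive, apart from any effect on infection.

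**Working it through.** The protocol gives no figure on this point to reproduce. The check is a reading of the rule, an enumeration, and an illustration on a stated assumption.

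**1. Items and their qualifiers (Section 1.3)**

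| Item | Change required by the wording? |
|---|---|
| Urgency | No |
| Frequency | No |
| Dysuria | No |
| Fever/chills | Not stated; acute by nature |
| Neurological condition | Yes (worsening) |
| Altered mental status | Implied (altered) |
| Incontinence | Yes (de novo) |

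No other section adds a qualifier. The word symptomatic in Section 3 does not help, because a long-standing symptom is still a symptom.

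**2. Which combinations qualify**

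- Pairs from seven items: 7 × 6 / 2 = 21.
- Pairs wholly within urgency, frequency and dysuria: 3 × 2 / 2 = 3.
- Pairs containing none of the three: 4 × 3 / 2 = 6, so 21 − 6 = 15 contain at least one.

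With a positive culture, the three wholly unqualified pairs meet the rule even if both symptoms have been present for years.

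**3. Fever/chills alone**

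Fever/chills is a single item, so culture plus fever/chills gives one symptom where two are required. Such an episode is not a UTI under Section 1.3. Section 6.3 nevertheless records hospital admission due to UTI and does not say whether an admission of this kind enters the primary count.

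**4. Size, on an assumption only**

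Let q be the share of counted episodes that are not new infections and do not respond to prophylaxis. The documents do not give q. Section 7 supplies a difference of 3 UTIs a year and an SD of 5.414. Assume the same q in each regimen before any effect, an unchanged SD, and a preventive effect on true infections only. The observable difference is then 3(1 − q). For a two-group comparison of means at two-sided 0.05 and 80% power, n per arm = 2 × (1.960 + 0.842)² × 5.414² / [3(1 − q)]². The last column assumes 785 / 5 = 157 per regimen.

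| q | Observable difference | n per arm, 80% power | Power with 157 per arm |
|---|---|---|---|
| 0 | 3.0 | 52 | 0.998 |
| 0.2 | 2.4 | 80 | 0.975 |
| 0.4 | 1.8 | 143 | 0.838 |
| 0.5 | 1.5 | 205 | 0.690 |

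Dilution alone leaves reasonable power for a 3-a-year difference until q is large. Power for smaller differences would suffer sooner. The table does not address bias from a q that differs between regimens.

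**The case against.** The best defence is that the protocol never says a scheduled culture is turned into a UTI. A reader might infer that a chronically symptomatic, colonised patient gains one counted UTI at every scheduled culture: 1 to 2 a year under Table 1, or 4 under the Section 6.3 list. The documents do not support this. Section 6.3 lists the patient-reported UTI count and the urine culture as separate items, and Section 2.2 gives cultures their own purpose, the evaluation of resistance. This objection stands, so no annual number of false episodes can be derived. Nor do the documents give any shares of such patients by regimen from which a spurious difference could be calculated.

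Second, Section 5 plans balance on neurological condition. That is a partial answer, because baseline bladder symptoms are not among the factors named.

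Third, requiring two symptoms is defensible. A reader might call the exclusion of fever alone an error. It is better seen as a trade-off, since counting every culture-positive fever would admit fever from other causes in colonised patients. Severe events are not lost either, because Section 6.3 records admissions, SOFA and SIRS. What remains is the unstated link between such admissions and the primary count.

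Fourth, one might read the culture's place in the list as allowing culture plus one symptom. That is strained: the culture is marked mandatory and is not a symptom.

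Finally, the rule cites an outside source that may require acute onset. The article states its own rule in full without that requirement, and sites will apply what is written.

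**Conclusion.** The point holds in a limited form. As written, Section 1.3 lets long-standing urgency, frequency or dysuria, any two together, meet the UTI definition with bacteriuria. This affects entry and, because no other definition is given, the primary outcome. The conclusion on wording is firm. The conclusion on consequence is conditional: it assumes that some participants have these symptoms as their usual state together with bacteriuria, and the documents give no frequency for this. Dilution or bias is possible, but its size is unknown.

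Separately, Sections 1.3 and 6.3 leave open whether an admission for UTI with fever/chills as the only symptom counts in the primary outcome. This is a gap to reconcile. It does not show that the two-symptom rule is wrong.

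**What to change.** 1. Amend Section 1.3 so that urgency, frequency and dysuria count towards a breakthrough infection only if new or worse than the patient's usual state.
2. Add a new-or-worse field for each symptom to the eCRF, completed for every episode, with an unknown option for episodes diagnosed elsewhere.
3. State that a positive scheduled culture without new or worse symptoms is recorded as bacteriuria.
4. State whether a hospital admission due to UTI that does not meet the two-symptom rule enters the primary count, so that Sections 1.3 and 6.3 agree. The choice is for the investigators.

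The cost is modest. Section 9.1 allows the eCRF to be revised without a protocol amendment, although the wording of Section 1.3 itself needs one. The observed UTI rate may fall below the planned 9.4 a year. Outside records may not document symptom onset. The Day 0 ACSS should not be assumed to show the usual state: entry requires a proven UTI, and Section 5 allows recruitment at visits after symptomatic infections. The usual state therefore has to be asked about directly. The change is best made early, because onset that is not recorded at the time is hard to reconstruct.

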### 1.4. Bacterial Spectrum in rUTI in NLUTD

There are very few publications on the specific bacterial spectrum in rUTI in NLUTD. Mainly the bacterial spectrum of complicated and nosocomial acquired UTI is taken as representative of rUTI as well [17].

Recent data show a similar bacterial spectrum to other populations suffering from rUTI. Most frequently, *Escherichia coli*, *Enterococcus faecalis*, *Klebsiella pneumoniae/variicola*, *Streptococcus viridans*, *Pseudomonas aeruginosa*, and coagulase-negative Staphylococci have been detected. To date, unfortunately, fluoroquinolones are the most frequently used antibiotic in the management of UTI, whereby no considerable increase in resistance could be observed. Identified *E. coli* strains showed a noteworthy resistance increase against amoxicillin/clavulanic acid from 26 to over 38% [18].

### 1.5. Management of rUTI in NLUTD

Treatment regimens in handling rUTI are highly individual and often challenging. Due to a lack of clinical information, grading of severity and, therefore, indication for antibiotic treatment is often unclear. Even though we usually have specific information concerning causative organisms for individual patients, empiric treatment regularly fails the patient. A multitude of antibiotic and non-antibiotic prophylaxis regimens have been tested to date, yet missing conclusive evidence [14,19,20,21].

### 1.6. Rationale

To our knowledge, there is limited evidence on prophylaxis to prevent rUTIs in NLUTD patients practising CISC. 

Long-term health outcomes and quality of life are significantly impaired in our population of interest, and increasing antibiotic consumption, as well as rising resistance rates against our antibiotic armamentarium, necessitates a controlled evaluation of non-antibiotic alternatives in the reduction of UTI frequency. Few trials support the use of non-antibiotic prophylaxis, but further investigation in a prospective manner is demanded eventually. If solid data supports any kind of named non-antibiotic alternative, this could serve to lower the burden on our healthcare system financially on the hand, and on the other hand, the even more pressing question of how to offer an evidence-based substitute in prophylaxis and therefore lowering exposure in the worldwide development of antibiotic resistance.

## 2. Objectives

The aim of this prospective observational cohort study is to investigate the impact of five different non-antibiotic prophylaxis regimens over the course of one year on predefined time points. Our long-term goal is to identify safe and effective candidate regimens that could be carried to a randomised controlled trial (RCT) to establish clinical and cost-effectiveness. 

### 2.1. Primary Objectives

To identify the clinical effectiveness of non-antibiotic prophylaxis regimens in the prevention of episodes of UTIs in NLUTD patients managing their bladder with CISC and having rUTIs. 

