## 3. Design

This is a prospective, longitudinal, multi-arm, multi-centre, observational, clinical cohort study. Patients will receive approved non-antibiotic UTI prophylaxis with either *Escherichia coli* viva OM-89 (UroVaxom^®^), bacterial lysate vaccine (StroVac^®^), nasturtium and horseradish root powder (Angocin^®^), D-Mannose or bladder irrigation with saline once daily. Occurring complications under named prophylaxis will be treated according to the current standard of care. 

Primary Outcome Measure: Incidence of symptomatic breakthrough infections.

Secondary Outcomes: Severity of infectious breakouts with antibiotic use, development of antibiotic-resistant (AMR) flora, number of antibiotics used, quality of life, and exploration of health economic assessment variables. 

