## 5. Patients Recruitment

Identification of observations: Patients to be observed will be identified through participating clinicians in either an outpatient setting, hospitalised patients or follow-up visits after symptomatic infections. The eligibility criteria checklist of all cases considered to be observed will be filled in by participating principal investigators (PI). Clinical information from the initial diagnosis should be used to assess eligibility.

A logbook of patient screening will be kept to keep track of the number of patients per unit who are eligible and who are not. We will also keep track of those who are eligible and refuse to participate. If recruitment rates are slower than the anticipated trajectory, the logbook will be reviewed to identify obstacles in recruitment. 

Patients will be stratified to balance our groups according to age, sex, underlying neurological condition and number of infections prior to study inclusion. 

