## 7. Statistical Considerations

Power analysis was performed to determine an adequate sample size. We considered that these patients suffer 9.4 UTIs per year with an SD of 5.414. Furthermore, we assumed that a reduction of 3 UTIs per year is clinically significant. In order to achieve an effect size of 0.1, 785 participants are necessary (power = 0.87; alpha = 0.05). Furthermore, to achieve an effect size of 0.2, 197 participants are necessary, or for an effect size of 0.3, 88 participants are required, respectively. Data measured on a continuous scale will be expressed as mean, standard deviation, range, and median. Counts and percentages of patients in the categories will be used to convey categorical data. When necessary, T- or Mann-Whitney tests will be performed to determine statistical differences in continuous variables, and Chi-square or Fisher’s tests will be used to test for statistical differences in categorical variables.

Patients with a minimum follow-up of 6 months who remained on the same prophylaxis regimen will be eligible for the final statistical analysis. 

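### The primary objective claims effectiveness in preventing UTIs with no untreated comparator, and any reading against the patients' selected entry year is biased by regression to the mean, by about 0.3 to 1.2 UTIs per year

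*Protocol article*

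**What the plan says.** The aim is stated in two ways. Section 1.1 gives a comparison: "The main aim of our study is to identify the comparative clinical effectiveness of non-antibiotic prophylaxis regimens". The Abstract also describes the aim as comparative. The formal primary objective in Section 2.1 reads "To identify the clinical effectiveness of non-antibiotic prophylaxis regimens in the prevention of episodes of UTIs in NLUTD patients" and names no comparator. The outcome is stated in Section 3: "Primary Outcome Measure: Incidence of symptomatic breakthrough infections".

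Section 7 takes a rate of 9.4 UTIs per year with SD 5.414 and continues: "we assumed that a reduction of 3 UTIs per year is clinically significant". The reference for that reduction is not given. For continuous variables, the only tests named there are the T-test and the Mann-Whitney test, without adjustment.

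No cohort is untreated. Section 4.1 lists as an inclusion criterion "Non-antibiotic prophylaxis with UroVaxom, StroVac, Angocin, D-Mannose or bladder irrigation with saline". The regimen is not randomised; the Abstract says: "The management protocols will be pre-defined, but the selection of the protocol will be at the clinicians’ discretion".

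Entry requires more than 3 infections in the last 12 months (Sections 4 and 4.1) and also "Microbiologically proven UTI according to Section 1.3", with no timing stated. Section 5 lists outpatient contact, hospital admission and "follow-up visits after symptomatic infections" as recruitment routes. Section 6.1 records each patient's UTI count for the last 12 months.

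**The concern.** Effectiveness in preventing UTIs means fewer UTIs than would have occurred without the regimen. With five treated cohorts, the study has no concurrent estimate of that quantity. Two references remain. One is the planning figure of 9.4, which comes from other patients. The other is the patient's own previous year, which is on the case report form and is the natural reading of a reduction.

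That previous year is not a neutral baseline. Patients are in the study because their count was above a threshold, and some enter because they have just had an infection. Both features push the entry-year count above the patient's usual rate, so the following year will tend to be lower whatever is given. Section 2 intends to carry effective candidates forward to a randomised trial. A before-after fall would not separate active from inert candidates.

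**Working it through.** **The plan's own sample size.** Inputs from Section 7: effect sizes 0.1, 0.2 and 0.3; N of 785, 197 and 88; alpha 0.05; power 0.87. With n = ((z for alpha + z for power) / effect size)², two-sided alpha 0.05 and power 0.80:

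- (1.960 + 0.842)² = 7.849
- 7.849 / 0.01 = 784.9, so 785
- 7.849 / 0.04 = 196.2, so 197
- 7.849 / 0.09 = 87.2, so 88

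The three totals match exactly at power 0.80. One-sided alpha 0.05 gives power 0.876 at 785, close to the stated 0.87. The same formula serves a one-sample test, a paired test and a 1-df chi-square test, so N does not reveal what a reduction is measured against. Nor does N follow from the 3 UTIs: an effect size of 0.1 is 0.1 × 5.414 = 0.54 UTIs, whereas 3 UTIs is 3 / 5.414 = 0.55 SD.

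**Apparent fall with no treatment effect.** Assume that each patient has a stable yearly rate, that rates follow a gamma distribution across patients, and that counts are Poisson given the rate.

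- Total variance: 5.414² = 29.31
- Between-patient variance: 29.31 − 9.4 = 19.91
- Year-to-year correlation: r = 19.91 / 29.31 = 0.679
- Expected next-year count after a prior-year count x: 9.4 + r(x − 9.4)
- Expected fall: (1 − r) × (mean prior-year count among entrants − 9.4), with 1 − r = 0.321

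More than 3 infections means a count of at least 4. There are three entry scenarios:

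1. *Entry at a random time.* Mean prior-year count 10.33, next year 10.03. Fall = 0.321 × 0.93 = **0.30**.
2. *Every patient enters at an infection counted in the look-back, with the chance of entry proportional to the rate.* Mean prior-year count 12.79, next year 11.70. Fall = 0.321 × 3.39 = **1.09**.
3. *As 2, but without weighting entry by rate.* At least 3 other infections are needed. Their mean is 9.92, so the prior-year count is 10.92 and the next year is 9.75. Fall = **1.17** (1.16 by simulation).

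Mixing scenarios 1 and 2:

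| Share entering at a counted infection | Fall (UTIs/year) | Share of the 3-UTI benchmark |
|---|---|---|
| 0% | 0.30 | 10% |
| 25% | 0.49 | 16% |
| 50% | 0.69 | 23% |
| 75% | 0.89 | 30% |
| 100% | 1.09 (1.17 in scenario 3) | 36% (39%) |

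**Sensitivity.** If 9.4 and 5.414 already describe patients selected on more than 3 UTIs, the threshold alone gives 0.55. If they are the entrants' own counts including the infection at entry, the fall is 1.41. If patients' rates vary over time, the threshold part of the base case rises from 0.30 to 0.46 at a year-to-year correlation of 0.5, and to 0.65 at 0.3.

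**The case against.** The strongest reply is that this criticises an analysis the plan does not contain. The primary outcome is incidence during follow-up, not change from baseline. Mann-Whitney compares independent groups, and no paired test is named. The Abstract and Section 1.1 state the comparative aim, Section 2 leaves clinical and cost-effectiveness to a later randomised trial, and Section 5 intends to balance the groups on prior infections. On this view Section 2.1 is shorthand.

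Much of this stands. A reader might infer that the study will test each regimen against its own entry year and will usually declare an inert one effective. The document does not support that: any such false-positive rate would belong to a test, and an equal split between arms, that the plan does not state. A reader might also infer that the study is sized on the 3-UTI reduction, but Section 7 ties 785 to an effect size of 0.1. It is also tempting to treat a fall above 1 UTI per year as the expected artefact. In the base case that needs nearly every patient to enter at a counted infection, while Section 4.1 fixes no timing and Section 5 lists other routes.

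What does not stand is that the wording is harmless. The formal primary objective and the meaning of the planning reduction are both stated in this document, and neither names a reference. The intention to balance groups sits beside clinician choice of regimen, and the tests named make no adjustment for prior count.

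**Conclusion.** The point holds as a fault in how the primary objective and the benchmark are stated. The design can address differences between regimens; it cannot show that any regimen prevents UTIs relative to no prophylaxis. Read against the entry year, a regimen with no effect would show a fall of about 0.3 UTIs per year from the threshold alone, about 0.7 if half the patients enter at a counted infection, and 1.1 to 1.2 if all do. That is roughly 10 to 40% of the benchmark. The artefact does not reach 3 under any reading examined, and the 3 UTIs are a planning assumption, not a success rule.

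The figures assume stable patient rates with Poisson variation, and that 9.4 and 5.414 describe patients before selection. The share entering at a counted infection is not in the document, so only the range is justified. Between-regimen comparisons share most of this bias if the cohorts have similar prior counts and entry routes. Clinician choice does not guarantee that.

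**What to change.** - **Section 2.1:** restate the primary objective as differences in UTI rate between the five regimens, in line with the Abstract and Section 1.1.
- **Section 7, analysis:** for the primary outcome, replace the unadjusted T or Mann-Whitney comparison with one adjusted for the prior-year UTI count. State that clinician choice of regimen leaves residual confounding.
- **Section 7, benchmark:** say what the 3-UTI reduction is measured against. It should not simply be relabelled as a 3-UTI difference between regimens, because nothing in the document supports that size of difference between active options.
- **Interpretation:** state that change from the entry year is descriptive and will not be used to call a regimen effective.

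The cost is wording in two sections and one covariate that Section 6.1 already collects. No extra arm, patients or data are needed. The downside is giving up an absolute effectiveness claim, which the design cannot support.
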